##### Analytical plan for second aim

To characterize potential non-linear patterns of CKD progression, we will implement analyses previously described by Li et al. [13] Briefly, we will initially apply a Bayesian smoothing technique to estimate each patient’s eGFR or proteinuria trajectory as a smooth curve. As such, its slope can be calculated month by month, accommodating a possible change in rate of progression over time [13]. We will then classify patients based on disease trajectory using iterative measures. This can be accomplished using two approaches. First, we plan to use latent class mixed effects models [14, 15] as described above. Second, the Bayesian smoothing technique [13] will allow us to estimate the “most likely” trajectory by the average of the generated Monte Carlo curves and the observed variation in curves around the mean estimated curve.

To quantify intra-individual variability in kidney function or damage, we propose to initially follow the approach previously taken by Al-Aly and colleagues [16]. We will define within-person variability as the coefficient of variation of a regression line fitted to all of the monthly fingerstick creatinine-based eGFR or bimonthly protein measures for each individual participant. The general concept of this approach is to calculate the deviation of the measured creatinine-based eGFR, for example, from its fitted value based on a linear regression model for each participant. This measure of kidney function variability has an advantage because it is normalized to the average value for each individual, which means it is a dimensionless metric that can be readily compared across participants who have different absolute levels of eGFR [16]. Furthermore, to improve the precision of the estimation of the intra-individual variability in kidney function or damage, we can take advantage of using the previously identified non-linear values while calculating variability. Depending on the question of interest, and the focus on either pathophysiology or prediction of disease, we will use logistic, failure-time, repeated measure or predictive analyses as described above. These measures of kidney function or damage will be defined over the course of 1 year for individuals, so the outcome assessment period in these models will begin at the end of the sub-protocol period or AKI episode.

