##### Monthly urine albumin testing

patients will receive urine diagnostic dipsticks and scan cards (Scanwell Health Urine Dipsticks and Scan Cards) and will be asked to download the “CRIC at Home” smartphone application. They will be asked to do the testing at home monthly for one year and weekly for two months of that year on the same day they perform the finger-stick creatinine test. At their clinic visit, we will describe the process to them. Patients will be asked to practice the test in the clinic before they leave to make sure they understand the process and to allow time for them to ask any questions. It will take about 15 min to learn how to perform the urine albumin testing at home.

Before performing the urine test, patients will be asked to complete a brief survey on risk factors for sudden changes in kidney function through the “CRIC at Home” smartphone application. For each test, they will first collect a urine sample in a specimen cup. After collecting the urine, patients will dip the urine diagnostic dipstick in the urine and then place on the diagnostic scan card and wait for the colors to develop. Using their smartphone, they will launch the “CRIC at Home” application and it will guide them through the process of taking a picture of the diagnostic scan card. After the application finishes scanning the picture, the test result will be displayed. The image and result are stored on the application. This application is unencrypted; however, only the patient’s result and unique ID are stored on the application and all study information will be removed after completion of the study. Once the patient has tested their urine, they will be asked to report the value by calling the AI-CRIC Study. Patients will discard the dipstick and scan card after completing the test.

We will give a printed schedule to patients at the clinic visit to remind patients when to perform the finger-stick creatinine and urine albumin tests. We may also call patients by telephone or contact them by email to remind them to perform these tests and let us know their results. A short questionnaire will also be given to patients to provide feedback on their experience with these home tests, which can be mailed back to us in a pre-paid envelope.

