Despite the strengths of the study, there are some potential pitfalls and limitations; we recognize that observed monthly changes in eGFR based on fingerstick creatinine measures may not reflect actual changes in underlying kidney function but rather variability in creatinine production. Our plan is to characterize potential non-linear eGFR trajectories over a 12 month testing period. With regards to urine albumin/protein excretion testing using the proposed urine diagnostic testing methods, there are well-known challenges in standardizing and accurately quantifying the amount of albumin or total protein by these methods. Nonetheless, the ability to detect the presence of and changes in semi-quantitative measures of urine albumin or protein has important potential clinical and prognostic implications. Furthermore, despite any measurement limitations, our study will provide key insights into the potential bimonthly variability in semi-quantitative urine albumin/protein excretion within the context of concurrent measures of eGFR. The total period of time during which each participant will wear the monitors is limited by features of the devices used (data storage capacity of the Zephyr BioPatch, and battery life in the ZIO XT Patch). While both devices will be worn long enough to capture diurnal variations, it is possible that some participants will wear the devices during periods in which the type and level of their activities are nonrepresentative. Finally, a larger number of patients may drop out from the study than we considered in the power calculations. The drop-out rate will be monitored and the enrollment target may be adjusted upwards.

In conclusion AI-CRIC study will help us to learn more about ESKD and its progression and relationship with CVD.

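### Aim 2 defines urine-protein variability as a coefficient of variation, but the home readings are semi-quantitative dipstick results, so the measure depends on the person's level and on unstated numeric codes

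*Protocol article*

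**What the plan says.** The Analytical plan for second aim gives one definition of within-person variability for both kidney function and kidney damage: the "coefficient of variation of a regression line fitted to all of the monthly fingerstick creatinine-based eGFR or bimonthly protein measures". The deviation is that of each measurement "from its fitted value based on a linear regression model for each participant", with eGFR given as the example. The stated advantage is that "it is normalized to the average value for each individual, which means it is a dimensionless metric that can be readily compared across participants"; the sentence goes on to specify participants at different absolute levels of eGFR. The approach is described as an initial one, and non-linear fitted values may replace the straight line.

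The section on monthly urine albumin testing describes a dipstick whose colours develop on a scan card and are read by a smartphone application. The Discussion refers to "changes in semi-quantitative measures of urine albumin or protein", concedes that these methods are hard to standardize and quantify, and still expects insight into "potential bimonthly variability in semi-quantitative urine albumin/protein excretion within the context of concurrent measures of eGFR".

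On frequency, the urine testing section says: "They will be asked to do the testing at home monthly for one year and weekly for two months of that year", on the same days as the fingerstick test. The Aim 2 analysis and the Discussion call the urine measures bimonthly.

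**The concern.** A coefficient of variation presumes a ratio scale: a true zero, meaningful distances and a mean that is not zero. Fingerstick eGFR meets this. Ordered dipstick categories do not, because their numeric values have to be assigned, and the article assigns none. The protein series in this definition can only be the home tests: other urine samples are taken at screening, at baseline and annually, whereas the variability measure is built over one year.

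Urine variability is a planned Aim 2 exposure, to be carried into logistic, failure-time, repeated-measures or predictive models. If its value is largely set by where a person sits on the dipstick scale and by how the scale is coded, an association with progression could be an association with albuminuria level. A reader of the results could not tell the two apart.

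**Working it through.** There is no plan figure to reproduce, since no stated sample size or power rests on this measure. The Aim 2 power statement (75 per group, difference 5, SD 9.05, two-sided 0.05) recomputes to 0.92, consistent with the stated value above 90%, and does not use it.

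**Inputs.** From the article: a per-person linear regression, division by the person's mean, dipstick readings. Assumed, because the article does not give them: ordered categories as the output, the numeric codes, and 12 readings (one per month, leaving out the extra weekly tests).

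**Formula.** CV = s / mean, with s = √(RSS / (n − 2)) about the person's fitted line.

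**Same one-step variability at different levels.** Take 12 readings alternating 0, 1, 0, 1, …:
- Total sum of squares = 12 × 0.25 = 3; Sxx = 143; Sxy = 3.
- RSS = 3 − 9/143 = 2.937; s = √(2.937/10) = 0.542.
- Ranks 0–4, means 0.5, 1.5, 2.5, 3.5: CV = 1.08, 0.36, 0.22, 0.15. The ratio of first to last is 3.5/0.5 = 7.
- Codes 0/30/100/300, same formula: 0.542 × 30/15 = 1.08; 0.542 × 70/65 = 0.58; 0.542 × 200/200 = 0.54. The ratio is 2.

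For codes a and b the CV is proportional to (b − a)/((a + b)/2), which depends only on b/a. The ratios between levels therefore do not depend on the number of readings. One-step toggling gives the same CV at every level only if the codes are a geometric sequence with a positive code for negative.

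**Five assumed codings.** Twelve readings toggling in the order 0, 1, 1, 0, …:

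| Codes | negative/trace | trace/1+ | 1+/2+ | 2+/3+ |
|---|---|---|---|---|
| 0–4 | 1.10 | 0.37 | 0.22 | 0.16 |
| 1–5 | 0.37 | 0.22 | 0.16 | 0.12 |
| 0/15/30/100/300 | 1.10 | 0.37 | 0.59 | 0.55 |
| 5/15/30/100/300 | 0.55 | 0.37 | 0.59 | 0.55 |
| log of the previous row | 0.28 | 0.12 | 0.17 | 0.12 |

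The same negative/trace record runs from 0.28 to 1.10, and participants change order: negative/trace is the most variable under ranks, 1+/2+ under 5/15/30/100/300. Six readings show the same pattern.

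**Floor.** All readings negative: 0/0, undefined, if negative is coded 0; exactly 0 if the code is positive. One trace among 11 negatives: 3.63 with ranks 0–4, 0.28 with ranks 1–5.

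**Equal true variability.** A continuous lognormal protein value (log SD 0.5, 12 readings, continuous CV about 0.50 at each level checked) was cut into five categories at assumed limits 10, 22, 60 and 200, with 2,000 draws per level. Mean CV at true medians 4, 8, 15, 30, 60, 120, 300:
- Ranks 0–4: 3.26, 1.67, 0.66, 0.33, 0.22, 0.15, 0.10. At the lowest level 66% are undefined and the mean is over the rest.
- 5/15/30/100/300: 0.17, 0.62, 0.52, 0.58, 0.59, 0.56, 0.31. At the lowest level 67% are exactly 0.

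The first falls throughout. The second rises from the lowest level, is roughly flat, and drops at the top.

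**Frequency.** Urine and fingerstick tests share the same days, so the two series have one frequency. The Aim 2 analysis nevertheless pairs monthly eGFR with bimonthly protein. Whether bimonthly means twice a month or every two months, it does not match monthly testing with two weekly months.

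**The case against.** The strongest reply has four parts.

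First, numeric coding is detail that a condensed article may leave to the full protocol or analysis plan. That is fair as to the codes. But the choice of a CV for protein is stated here, and only a particular (geometric) set of codes would equalize one-step changes across levels. Even then the chosen ratio sets the size of the CV, and the floor at all-negative remains.

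Second, the approach is called initial, non-linear fits are allowed, and the Discussion admits the measurement limits. These stand as mitigation, but a non-linear fit changes only the numerator; the division by the mean stays.

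Third, the models could adjust for level. That would reduce confounding with level but would not remove the dependence on coding.

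Fourth, the impact is limited: the Aim 2 analysis singled out for power uses trajectory classes and eGFR slope, and proteinuria trajectories have a separate smoothing analysis. That stands.

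A reader might also infer stronger points that the article does not support:
- That all-negative participants would be dropped. This needs negative coded 0, which is not stated.
- That low albuminuria would always look most variable, so that the measure is albuminuria with its sign reversed. This holds for ranks from 0; with 5/15/30/100/300 the lowest level looks least variable.
- That a seven-fold distortion is general. It belongs to ranks 0–4; with 0/30/100/300 the range is two-fold.
- That the article claims comparability for urine protein. Its claim that "it is a dimensionless metric that can be readily compared across participants" is confined to levels of eGFR. It is not wrong for protein; it simply lends protein no support.

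**Conclusion.** The point holds in limited form. The article prescribes a ratio-scale statistic for data it describes as semi-quantitative, and the result depends on the person's level and on codes it does not state. For identical one-step toggling the CV varies two-fold (0/30/100/300) to seven-fold (ranks 0–4) by level. For one fixed negative/trace record it varies from 0.28 to 1.10 across five codings. The direction of the dependence on level also changes with the coding, so the direction of any resulting bias cannot be stated in advance.

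This rests on the assumption that the application returns ordered categories, and on assumed codes and cut-points. The share of participants near the floor is unknown. One Aim 2 exposure is affected; the stated power figures and the Aim 1 comparisons are not. It should be changed before the analysis, but it does not threaten the study as a whole. The frequency conflict is real, secondary, and no part of the case against the CV.

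**What to change.** Restrict the CV to fingerstick eGFR. For dipstick results, specify an ordinal measure of variability: for example, the proportion of consecutive tests that change category, or within-person variability from an ordinal mixed model. Adjust outcome models for the person's median category. The proportion of changes is also 0 for an all-negative participant, but it needs no numeric codes and no division by the mean, and it reads plainly as no observed change; the adjustment for level is what guards against the floor.

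The cost is a change of analysis wording and a different model for one exposure, with no new data. The downside is that the urine and eGFR measures are no longer on a common scale.

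Separately, reconcile the urine test frequency between the urine testing section, the Aim 2 analysis and the Discussion. It fixes the number and spacing of readings behind whichever measure is used.

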##### Sample size and power considerations for second aim

are based on the event rates in the parent CRIC study. As outlined above, a variety of analyses will be performed. We therefore highlight an analysis of particular interest for this aim: one where we extract classes of specific nonlinear patterns of kidney function from the ambulatory monitoring data and then use those classes to predict differences of eGFR slope in the subsequent year. For these assessments, the clinically meaningful differences that we hope to detect are one-year eGFR changes between two non-linear trajectory groups of 5 ml/min/1.73 m2. Even when comparing two groups of nonlinear kidney function patterns, each comprising 15% of the participants, with 500 participants we will have greater than 90% power to detect differences in one-year changes in eGFR of at least 5.0 ml/min/1.73 m2 between groups. This power approximation was accomplished using a two-sided, 0.05 level, two-sample t-test with groups of 75 individuals each, whose within-person variability of one-year changes in eGFR was no greater than 9.05 ml/min/1/73 m2. This demonstrates that with data from 500 participants we will be able to assess clinically meaningful questions in this specific aim.

##### Analytical plans for third aim

We will examine the distribution of newly-identified features related to heart rate, physical activity and heart rhythm abnormalities and how they change over time. We will fit linear or generalized linear mixed models depending on the type of the measures (either continuous, binary or categorical form). These models naturally handle multiple repeated observations from the same individuals by introducing a within subject correlation structure. We will use these models to compare the distribution of different features across subgroups defined by demographic information and standard and novel CV risk factors. We are also interested in whether these features are risk factors and predictive of future clinical outcomes. We will test the hypothesis whether a candidate predictor is a risk factor for clinical outcomes including CV events and CKD trajectories/progression. We will fit Cox proportional hazards models for survival outcomes, e.g., time to heart failure (HF) and time to halving of eGFR, ESKD, and death. We will adjust for confounding factors, including demographic characteristics and traditional and novel CV risk factors, in a stepwise fashion. More specifically, we will start with a model including the candidate predictors derived from the biosensor data and demographic information only. We will then sequentially add traditional and novel CV risk factors to the model. Statistical issues, including potential violations of the proportional hazards assumption and competing risks due to death, will be handled in the same way as described above. We will also evaluate the added predictability of outcomes beyond standard risk factors. Metrics that will be used to quantify the added predictability include the C statistic, Net Reclassification Index, and Integrated Discrimination Index. Confidence intervals for these metrics will be derived using cross-validation and bootstrap resampling.

Sample size and power considerations for third Aim: are based on the event rates in the parent CRIC study. With 500 participants, we will have 80% power to detect HRs of 1.82, 1.91, or 2.74 for the risk of HF or atrial fibrillation associated with the presence of specific nonlinear patterns of CV health if these patterns are observed in 50, 30% or 10% of participants, respectively. As long as a pattern associated with CV events of CKD progression is present in greater than 10%, we will have statistical power to detect clinically meaningful HRs of 2.0.

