##### Follow-up visits

We expect to follow participants from 30 to 54 months, depending on date of enrolment. We will repeat baseline measurements and observations annually. We will contact all participants six months after each of these visits to update contact information, ascertain interim outcome events, and assess health resource utilization. We will conduct follow-up visits at 11 to 13-month intervals.

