Higher mortality rate [32, 33], higher risks of HF [34, 35], heart rate variability (HRV) [36], peripheral arterial disease [37–39], and stroke [40] are reported in patients with CKD. Among CRIC study participants, the overall incidence of HF was 21.7 per 1000 person-years and 18.6% of participants developed incident peripheral arterial disease during 6.3 years of follow-up [41]. Left ventricular hypertrophy is very common in CKD patients. CRIC showed that left ventricular mass index was strongly associated with incident hear failure, even after adjustment for CVD risk factors and biomarkers [42]. Likewise, CRIC reported that low eGFR was strongly associated with greater coronary artery calcification and significantly predicted the risk of CVD [43, 44]. American Indian participants in the SHS had a higher prevalence of sub-clinical cardiac abnormalities on echocardiogram, including left ventricular hypertrophy, left atrial dilation, and reduced left ventricular systolic and diastolic function [45]. HRV in a variety of clinical settings has been used to predict death and HF [46, 47]. To the best of our knowledge, little is known about the prognostic value of biometric monitoring in CKD. In particular, using such monitoring to detect individuals with limited CV reserve prior to a CV event may provide novel opportunities to implement preventive interventions. With AI-CRIC, we will use remote biometric monitoring to measure HRV as an indicator of limited CV reserve. In the CRIC Study even limited data showed that HRV is associated with mortality [48]. Thus, our goal is to test the hypothesis that wearable biosensor technologies can provide robust measures of HRV in CKD patients. This test will enable us to detect a subset of CKD participants at higher risk for HF as candidates to subsequently test the value of intervention programs.

Many previous studies demonstrated the relationship between diabetes, obesity, and hypertension in persons with chronic kidney disease. RAASI treatment correlates with subsequent reduction in the rate of ESKD [49, 50]. The prevalence of hypertension in CKD varies by race, etiology of CKD and GFR [5]. Considering the fact that there are currently no markers available to predict the subsequent loss of kidney function in AI patients already treated with RAASi, in the AI-CRIC study we will investigate such markers.

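### Aim 3's 80%-power hazard ratios imply about 87 events; at the parent-cohort heart-failure rate quoted in the article they cannot apply to heart failure alone, and the endpoint they do apply to is not pinned down

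*Protocol article*

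**What the plan says.** The paragraph on sample size and power for the third aim (Protocol article) says that its calculations "are based on the event rates in the parent CRIC study". It then gives one set of hazard ratios: "With 500 participants, we will have 80% power to detect HRs of 1.82, 1.91, or 2.74 for the risk of HF or atrial fibrillation". The three values belong, in order, to cardiovascular patterns carried by half, 30% and 10% of the cohort. The paragraph states no event count, event rate, follow-up time or significance level.

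The article gives the other relevant facts elsewhere:

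- **HF rate.** The Discussion reports that among CRIC participants "the overall incidence of HF was 21.7 per 1000 person-years".
- **Follow-up.** The Follow-up visits section says "We expect to follow participants from 30 to 54 months, depending on date of enrolment". The Study timeline section allows up to 60 months for people recruited in the first year.
- **Aim 3 outcomes.** The analysis text gives, as examples of survival outcomes for Cox models, "time to heart failure (HF) and time to halving of eGFR, ESKD, and death". AF is not mentioned there. Table 1 lists heart-failure hospitalization and serious arrhythmia as separate cardiovascular outcomes and does not name AF.

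**The concern.** The power claim is attributed to parent-CRIC event rates, yet the one HF rate that the article takes from CRIC is less than half of what the stated hazard ratios require. HF is the first survival outcome named for Aim 3. The Discussion also gives the purpose of the biosensor work as finding participants at higher risk of HF. If readers take the 80% figures to cover HF, a null HF result would be read as coming from an adequately powered analysis when, on the article's own rate, it would not be.

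**Working it through.** **Inputs**

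- N = 500; 80% power; hazard ratios (HR) 1.82, 1.91 and 2.74 at pattern prevalence p = 0.5, 0.3 and 0.1 (Aim 3 power paragraph).
- HF rate 0.0217 per person-year (Discussion).
- Follow-up 30 to 54 months (Follow-up visits), 60 months at most (Study timeline). Assumption: mean of 42 months (3.5 years), the midpoint of 30 and 54.
- Assumption: two-sided 0.05. The article states this for Aim 2 only.
- Assumption: no dropout, and person-time counted from enrolment.

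**Step 1: events implied by the stated hazard ratios**

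Schoenfeld's formula is D = (1.960 + 0.842)² / [p(1 − p)(ln HR)²], with numerator 7.849.

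- HR 1.82, p = 0.5: 7.849 / (0.25 × 0.3586) = 87.5
- HR 1.91, p = 0.3: 7.849 / (0.21 × 0.4187) = 89.3
- HR 2.74, p = 0.1: 7.849 / (0.09 × 1.0160) = 85.8

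The three agree closely, so a single count of about 87 events appears to lie behind them. As a check, 87 events give 80%-power hazard ratios of 1.82, 1.93 and 2.72, which nearly reproduces the article's figures.

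**Step 2: HF events expected**

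Expected events = 500 × years × 0.0217. At 3.5 years this is 38.0 (36.6 if allowance is made for people leaving the risk set after an event).

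**Step 3: power and detectable hazard ratios for HF alone**

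Power = Φ(√[D p(1 − p)] × ln HR − 1.960). For D = 38 and p = 0.5: √9.5 × 0.599 − 1.960 = −0.11, so power is 45%. The 80%-power hazard ratio is exp(2.8016 / √[D p(1 − p)]).

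| Follow-up for all 500 | HF events | Power at HR 1.82 / 1.91 / 2.74 | HR detectable with 80% power at p = 0.5 / 0.3 / 0.1 |
|---|---|---|---|
| 30 months | 27 | 34% / 34% / 35% | 2.93 / 3.23 / 6.01 |
| 42 months | 38 | 45% / 45% / 46% | 2.48 / 2.70 / 4.55 |
| 54 months | 49 | 55% / 55% / 56% | 2.23 / 2.40 / 3.81 |
| 60 months | 54 | 60% / 59% / 61% | 2.14 / 2.29 / 3.55 |

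Reaching 87 HF events at this rate would take 87 / (500 × 0.0217) = 8.0 years for everyone.

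**Step 4: more favourable variants for HF alone**

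- One-sided 0.05: 57% to 59% at 3.5 years, 71% to 72% at 60 months.
- 0.0217 read as the rate in people without the pattern, so that events are multiplied by (1 − p) + p × HR: 52% to 59% at 3.5 years, 63% to 70% at 54 months, 67% to 75% at 60 months.
- Both together, with all 500 followed for 60 months and none lost: 84% / 79% / 78%. Only the 50%-prevalence case passes 80%, and only with every assumption set in its favour.

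**Step 5: what a composite would need**

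At 3.5 years, 87 / (500 × 3.5) = 0.0497 per person-year. Less 0.0217 for HF, AF would have to add 0.028, or about 28 first events per 1000 person-years. The addition needed is 48 per 1000 at 30 months (0.0696 − 0.0217), 17 at 54 months (0.0387 − 0.0217) and 13 at 60 months (0.0348 − 0.0217). At 3.5 years, an addition of 10 per 1000 gives power of about 60% to 61%, 20 gives 72% to 73%, and 30 gives about 81% to 82%.

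**The case against.** The strongest reply is that HF alone is not the endpoint in the power sentence. It speaks of HF or AF, and one set of hazard ratios from one event count fits a composite at least as well as two separate outcomes, which would normally have different rates. Table 1 includes serious arrhythmia, and Aim 3 studies heart rhythm, so both components have a place in the study. The list of Cox outcomes is illustrative, so its silence on a composite does not show that none is intended. This stands. A reader might infer that Aim 3's power is 45% and not 80%; the documents do not support that, because they give no AF or combined rate, and 80% cannot be disproved for a composite.

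A second reply is that 21.7 per 1000 is an overall CRIC figure given as background, while this cohort is described as diabetic and may have more HF. The planning rate may therefore differ. But HF alone would need about 87 / 38 = 2.3 times the quoted rate at 3.5 years, and the article says that it planned on parent-CRIC rates without giving another.

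A third is that a condensed article may leave event rates and significance level to the full protocol. Their absence alone would indeed be no finding. The point here is that a stated power figure does not fit the one relevant rate the article reports, if it is read as applying to HF.

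**Conclusion.** The point holds for HF on its own. The stated hazard ratios need about 87 events, and HF at the quoted rate supplies about 38 (27 to 54 over follow-up of 30 to 60 months). Power for HF alone at the stated hazard ratios is about 45% (34% to 61%). Detectable hazard ratios at 80% power are about 2.5, 2.7 and 4.6, and still about 2.1, 2.3 and 3.6 if everyone were followed for 60 months.

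This rests on a two-sided 0.05 test, a 3.5-year mean, no dropout, and the quoted rate applying to this cohort. Dropout, or person-time starting only after a pattern has been measured, would lower the HF figures further.

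It is not shown that the 80% claim is false for a composite of HF or AF. What is shown is that the figures either do not hold for HF at the quoted rate, or belong to an endpoint that the Aim 3 analysis text and Table 1 do not name. Either way the power paragraph needs correction.

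**What to change.** 1. In the Aim 3 power paragraph, say which endpoint the 80% figures apply to, and give the event rate, follow-up and significance level used.
2. If it is a composite of HF or AF, name it as a survival outcome in the Aim 3 analysis text and give the combined rate.
3. In either case, report detectable hazard ratios for HF alone: about 2.5, 2.7 and 4.6 at the quoted rate and 3.5 years, or values recomputed from the sponsor's actual planning rate. Do not claim 80% power at 1.82, 1.91 and 2.74 for HF alone unless that rate supports it.

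The cost is a few sentences and one recalculation. Design, sample size and data collection are untouched.

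### Aim 3 claims power for a hazard ratio of 2.0 at any pattern prevalence above 10%, but its own figures put 80% power for 2.0 only near 25% prevalence

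*Protocol article*

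**What the plan says.** Both statements stand in the power paragraph for the third aim, at the end of the section headed Analytical plans for third aim in the Protocol article.

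- The calculation: "we will have 80% power to detect HRs of 1.82, 1.91, or 2.74 for the risk of HF or atrial fibrillation", "if these patterns are observed in 50, 30% or 10% of participants, respectively". At 10% prevalence the HR detectable with 80% power is therefore 2.74, and at 30% it is 1.91.
- The conclusion, in the next sentence: for a pattern linked to cardiovascular (CV) events or CKD progression (the text prints 'of', apparently for 'or') that is "present in greater than 10%, we will have statistical power to detect clinically meaningful HRs of 2.0".

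The paragraph says that its figures "are based on the event rates in the parent CRIC study", but it gives no event rate, event count, significance level or formula. The first-aim power section takes a two-fold difference in risk as clinically meaningful and uses 80% as its benchmark for power.

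**The concern.** The conclusion does not follow from the calculation before it. Power falls as the effect gets smaller. A prevalence at which 2.74 is only just detectable with 80% power therefore cannot give 80% power for 2.0. From the stated figures alone, the prevalence at which 2.0 becomes detectable with 80% power lies between 10% (where 2.74 is needed) and 30% (where 1.91 suffices).

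This sentence is the closing power claim for one of three specific aims, and 2.0 is the effect that the protocol itself calls meaningful. Someone who relies on it when interpreting a pattern seen in 10% to 20% of participants would overrate what a non-significant result says about a two-fold risk.

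**Working it through.** **Inputs.** From the Aim 3 paragraph: 500 participants, 80% power, and the pairs (50%, 1.82), (30%, 1.91) and (10%, 2.74). Assumed: two-sided 0.05, which the article states for Aim 2 ("using a two-sided, 0.05 level, two-sample t-test with groups of 75 individuals each") but not for Aim 3. The number of events is not given and is solved from the pairs.

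**Step 1: reproduce the plan's figures.** Schoenfeld's formula with pattern prevalence p is

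D = (1.960 + 0.8416)² / [p(1−p)(ln HR)²], with numerator 7.849.

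- HR 1.82, p = 0.50: 7.849 / (0.25 × 0.3586) = 87.5 events
- HR 1.91, p = 0.30: 7.849 / (0.21 × 0.4187) = 89.3 events
- HR 2.74, p = 0.10: 7.849 / (0.09 × 1.0160) = 85.8 events

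The three agree within about 4%. A single count of 87.5 returns detectable HRs of 1.82, 1.92 and 2.71. The calculation sentence is therefore coherent, and the fault lies in the conclusion.

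**Step 2: power for HR 2.0.** Power = Φ(√[D p(1−p)] × ln 2 − 1.960). At p = 0.10 and D = 85.8: √(85.8 × 0.09) = 2.779; 2.779 × 0.6931 = 1.926; 1.926 − 1.960 = −0.034; Φ = 0.487.

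| Prevalence | D = 85.8 | D = 87.5 | D = 89.3 |
|---|---|---|---|
| 10% | 48.7% | 49.4% | 50.2% |
| 11% | 52.0% | 52.7% | 53.6% |
| 15% | 63.0% | 63.9% | 64.8% |
| 20% | 72.8% | 73.7% | 74.5% |
| 25% | 79.4% | 80.2% | 81.0% |
| 30% | 83.7% | 84.4% | 85.1% |

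**Step 3: prevalence needed for 80% power.** Solve p(1−p) = 7.849 / (D × 0.4805). For D = 87.5 the right-hand side is 0.187, so p = 0.248. Over the three counts p runs from 0.241 to 0.256. Because p(1−p) is symmetric, the range with at least 80% power is roughly 25% to 75%. At 10% prevalence the events needed are 7.849 / (0.09 × 0.4805), or 182, which is 36.4% of 500.

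**Step 4: sensitivity at 10% prevalence.**

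- One-sided 0.05, with events re-solved to 68 to 70: 53% to 54%.
- Baseline hazard held fixed, so that fewer events occur at HR 2.0 (70 to 82): 41% to 47%.
- Freedman's formula solved from the 10% pair: 41%. Solved from the 30% or 50% pair it gives 65% or 75%, but the three pairs then imply 40, 73 and 93 events, so this formula does not fit the plan's figures together.

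No variant reaches 80%.

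**The case against.** Several points can be made for the sentence as printed.

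- **It names no power level.** True, but the only level in the paragraph is 80%, one sentence earlier, and the first-aim section uses the same benchmark. Reading 80% across is natural, though it remains a reading.
- **It says greater than 10%, and 49% belongs to exactly 10%.** This stands as a limit on the 49%, which is the edge of the claimed range. It does not rescue the claim, because power is still 52% to 54% at 11% and stays below 80% until about 25%.
- **The significance level and event count are not stated.** This stands. A reader might take 49% as the true power, but the article supports only a conditional estimate of about one half.
- **The sentence also covers CKD progression, which may produce more events.** This stands in part. The first-aim section says that CKD progression rates in CRIC exceed 0.02 per year, but the Aim 3 paragraph gives no figure for them. A reader might extend the shortfall to CKD progression; the article does not show that. The sentence still fails for the CV events it names.
- **The correct figure of 2.74 is printed just before.** A careful reader can see the limit, and nothing in the article derives the target of 500 from the closing sentence. That bears on how serious the error is, not on whether it is one.

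**Conclusion.** The closing sentence is wrong as written for HF or atrial fibrillation. That conclusion needs no assumption beyond reading 80% as the intended power. Its size rests on Schoenfeld's formula, two-sided 0.05 and 86 to 89 back-solved events. Power for HR 2.0 is then about one half at 10% prevalence (roughly 41% to 54% across the assumptions that fit), and the prevalence threshold is too low by a factor of about 2.5.

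Three further inferences are tempting and are not supported.

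- **That the study expects about 87 events.** The count only makes the stated HRs agree. The Discussion gives an HF incidence of 21.7 per 1000 person-years, and follow-up is 30 to 54 months. Without allowance for depletion or dropout, that is 500 × 2.5 × 0.0217 = 27 to 500 × 4.5 × 0.0217 = 49 HF events. Nor does this prove the stated HRs wrong, since they concern HF or atrial fibrillation and no atrial fibrillation rate is given.
- **That most patterns of interest will have a prevalence of 10% to 25%.** The article gives no expected prevalence for any pattern.
- **That the sample size or design is unsound.** The error is in one summary sentence, and correcting it changes no design element.

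**What to change.** Replace the closing sentence with one that agrees with the stated HRs, for example:

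> For HF or atrial fibrillation, 80% power for an HR of 2.0 requires the pattern in roughly 25% to 75% of participants; at 10% prevalence the detectable HR is 2.74 and power for an HR of 2.0 is only about one half.

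The authors should check the prevalence range and the power against their own calculation, since the significance level and event count behind the HRs are not printed. No event count should be inserted unless they confirm it. A claim about HR 2.0 for CKD progression should stay only if it is supported by its own stated event rate.

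The cost is one sentence and a less favourable power statement. Sample size, procedures and analysis are unchanged.
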